### Research instruments

The instruments were developed by the study investigators and reviewed by the project’s Research Advisory Committee (RAC) (Additional file 1). The school quality tool is based on the Kenya Ministry of Education, Science and Technology school census tool for their Education Management and Information System. It includes information on school enrollment, number and education level of teachers, access to water and sanitation facilities, provision of sanitary pads, etc. These quality measures will later be accounted for in the analysis as a mediating factor in the relationship between the intervention and schooling outcomes.

A quantitative survey for girls was administered at baseline in the first quarter of 2017, and a similar survey will be administered after 18-21 months (Additional file 2). The survey covered topics such as: household socio-demographic characteristics, education participation, gender norms, social assets and networks, self-efficacy, locus-of-control, savings and livelihoods, marital and child-bearing experiences, menstruation experiences, experience of physical and sexual harassment and violence, reproductive health knowledge, HIV and AIDS risk perception, sexual behavior, comprehension in Swahili and English, mathematics assessments, and cognitive testing. The endline survey will include additional questions to measure exposure to interventions. The surveys were translated into Swahili and pilot-tested prior to the start of data collection and revised based on feedback from interviewers before data collection begins.

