## Methods/design

The Nia Project interventions are implemented by ZanaAfrica and Plan International, Kenya. Girls enrolled in Class 7 at the start of the 2017 school year are the beneficiaries, receiving interventions over a period of 5 school terms, from May 2017 to December 2018. The Nia Project includes two intervention components: 1) provision of Nia brand disposable sanitary pads, and 2) reproductive health education, including menstrual hygiene management as an extracurricular program for girls enrolled in school.

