### Cluster randomized study design

The design for the evaluation of the Nia Project is a longitudinal, cluster-randomized controlled trial consisting of a baseline survey with a cohort of Class 7 girls, a school quality survey, qualitative data collection, school attendance tracking, and an endline survey at the completion of the 18-month intervention period with the same cohort. The study involves 140 public primary schools (35 schools per arm) in three rural sub-counties (Magarini, Kaloleni and Ganze) of Kilifi County in the Coastal area of Kenya. Before program implementation, the schools were stratified by sub-county and randomly assigned to one of the following four study arms (See Fig. 1):Control group;Sanitary pad distribution;Reproductive health education; orSanitary pad distribution + reproductive health education.

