### Study sites

The sub-counties and schools were selected in collaboration with the Kilifi County Department of Education, Ministry of Education, Science and Technology. Within the three sub-counties (Magarini, Kaloleni and Ganze), all schools with 25 or more girls in Class 7 were eligible for the study. A total of 215 schools were mapped, and a 1000 m buffer was created around each school. For schools with overlapping boundaries, one school was randomly selected. This resulted in a list of 173 schools with at least 25 girls in Class 6 or in Class 7 in 2016. A listing exercise was conducted to verify enrollment and school type in the first quarter of 2017. Based on this data, 25 schools were excluded because they did not meet the minimum criteria of 25 girls in Class 7, and an additional seven were excluded because they were determined to be boarding schools. Subsequently, one school in Magarini was excluded after it was closed indefinitely by the Department of Education during baseline data collection. This resulted in 140 schools – 44 in Magarini, 50 in Kaloleni and 46 in Ganze.

In schools with 25 girls in Class 7, all girls were included in the research sample. In schools with a larger number of girls, 25 girls were randomly selected for the research sample and five additional girls were selected as alternates. Of the expected 3500 girls, a total of 3489 girls were interviewed as part of the baseline survey. All Class 7 girls, including those who were not in the research sample, are eligible to receive interventions. At the completion of data collection in each sub-county, stakeholder meetings were held and schools within that sub-county were randomly assigned to one of the four study arms through a public lottery.

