### Analysis plan

The program evaluation of the Nia Project will examine the effect of the average treatment across study arms while identifying the causal mechanisms driving that impact. Using intent-to-treat analysis, all girls in the original sample randomized to study arms will remain part of the study despite non-compliance, protocol deviations, withdrawal, or anything else that happens after randomization. Econometric estimation techniques such as fixed effects estimation will be applied to control for unobserved time invariant individual characteristics. The evaluation will compare the average increase in outcomes of girls in intervention arms to the average increase in outcomes of girls in the control arm. Additional hypotheses will be tested using difference in difference analysis to understand both causal mechanisms among girls who received the interventions and the potential effect of improvements in short-term indicators on longer-term outcomes. The rich dataset will provide an extensive list of variables that can be adjusted for directly in the analysis. The results will be triangulated using qualitative data.

To examine balance across study arms following randomization, multinomial logistic regression models were estimated using each dataset to test for joint orthogonality for a selected list of indicators, comparing each treatment group with the control group. For the school quality dataset, the variables included were: school performance by gender, number of toilets, distribution of pads and availability of pads in stock. The results showed that there were jointly no significant differences between study arms (*p* = .60). For the girls’ dataset, indicators included were: ever repeated a grade, age at starting school, self-efficacy scale, decision-making scale, gender-norms scale, reproductive health knowledge score, ever menstruated, justification of violence, experience of symptoms of reproductive health infections and ever had sex. The results showed that there were jointly no significant differences between study arms (*p* = 0.14).

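### School quality, apparently measured once before the interventions, is given the role of a mediator; it can only be a baseline covariate or an effect modifier

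*Protocol article*

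**What the plan says.** The Research instruments section describes a school quality tool that covers "school enrollment, number and education level of teachers, access to water and sanitation facilities, provision of sanitary pads, etc". It then gives these data their analytic role: "These quality measures will later be accounted for in the analysis as a mediating factor in the relationship between the intervention and schooling outcomes".

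Four other places in the article bear on when the data were collected and how they are used:

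- Cluster randomized study design lists the components that follow the baseline survey as "a school quality survey, qualitative data collection, school attendance tracking, and an endline survey". One school survey appears, and no repeat is described.
- Study sites puts allocation after fieldwork: "At the completion of data collection in each sub-county, stakeholder meetings were held and schools within that sub-county were randomly assigned".
- Methods/design gives the programme period, with girls "receiving interventions over a period of 5 school terms, from May 2017 to December 2018".
- Analysis plan reports a completed balance check: "To examine balance across study arms following randomization, multinomial logistic regression models were estimated using each dataset". It then names the school items: "For the school quality dataset, the variables included were: school performance by gender, number of toilets, distribution of pads and availability of pads in stock". A joint test gave p = .60.

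**The concern.** A mediator is a variable that the intervention changes and that in turn changes the outcome. A characteristic fixed before allocation cannot be changed by allocation. The article treats one dataset as unaffected by arm when it tests balance, and as lying on the path from arm to schooling outcome when it describes the instrument. Both cannot be true of the same measurements.

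The Analysis plan says that the evaluation will identify the causal mechanisms behind the impact. An analyst who followed the Research instruments sentence literally would look for part of the effect passing through toilets, teachers or enrolment as they stood at the start. Whatever was found would be noise. The same variables have two legitimate uses, baseline adjustment and a look at whether effects differ by school conditions, and the stated role points to neither.

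**Working it through.** **Step 1: timing.** The article does not date the school survey. Three statements place it before the interventions:

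- A balance check is meaningful only for variables that allocation could not have affected, and the school data were used for one.
- Schools were allocated after data collection in their sub-county. Study sites does not say in so many words that this includes the school survey.
- Only one school survey is listed, whereas Research instruments says explicitly that a similar girls' survey will follow at 18 to 21 months.

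Together these support a strong inference, not a printed fact.

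**Step 2: the expected indirect effect.** Write the indirect effect as a × b, where a is the arm difference in school quality and b is the slope of outcome on quality given arm. If quality is fixed before randomisation, the true a is 0, so the true indirect effect is 0 whatever b is. This needs no numerical assumption. The theory of change, as described in the text, agrees: it runs through pad use, knowledge and attitudes, gender norms and self-efficacy, and names no effect of the programme on school quality.

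**Step 3: how far a chance estimate could stray (illustration).** The plan gives no figure of its own to reproduce on this point.

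Inputs from Sample size calculations: 35 schools per arm, ICC 0.173, SD 3.57 days, detectable difference 1.18 days. Assumed: a correlation of 0.3 to 0.5 between school quality and the school component of the outcome, and an outcome analysed at one time point.

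- SD of the chance arm difference in a standardised school variable: sqrt(2/35) = 0.239.
- Between-school SD of days missed: sqrt(0.173) × 3.57 = 1.485 days.
- SD of the spurious indirect effect: 0.239 × 1.485 × 0.3 = 0.11 day, and 0.239 × 1.485 × 0.5 = 0.18 day.
- Relative to 1.18 days: 9% and 15%.

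**Step 4: cross-check by simulation.** School means were simulated for 35 against 35 schools with 20 girls each, a total effect of −1.18 days and 4,000 runs. Quality was assumed to explain 10%, 30% or 50% of the variance of school means, which differs from the assumption in step 3.

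| Assumed R² | Mean indirect effect (days) | SD of indirect effect (days) | SE of arm effect, unadjusted | SE, quality as baseline covariate |
|---|---|---|---|---|
| 10% | 0.00 | 0.13 | 0.40 | 0.38 |
| 30% | 0.00 | 0.22 | 0.39 | 0.33 |
| 50% | 0.00 | 0.28 | 0.40 | 0.29 |

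The indirect effect centres on zero in every case. Used as a plain covariate, quality left the arm effect at about −1.18 days and reduced its standard error.

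**Step 5: the estimator named in the Analysis plan.** That section proposes fixed effects for time-invariant individual characteristics, and difference-in-difference analyses. A school variable measured once is constant over time for each girl who stays in her school, so individual fixed effects absorb its main effect. In those models it can enter only through interactions with time. The figures in steps 3 and 4 do not carry over, because they would need the between-school SD of change, which the article does not give.

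**The case against.** The strongest reply is that this is one loosely chosen word. The article specifies no mediation model, no indirect effect and no decomposition; it says only that the measures will be accounted for. The Analysis plan speaks of variables that can be adjusted for directly, and does not list school quality among the mechanisms. If the authors meant adjustment or moderation, the likely analysis does no harm and may gain precision. Even a formal mediation analysis would produce an estimate with its own standard error, so a false claim of mechanism would not routinely follow. Much of this stands, and it limits the point to the stated role of the variables. It does not remove the point, because adjustment, moderation and mediation are three different models and the text names the one that cannot apply.

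A reader might infer two stronger things that the documents do not support.

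- That the trial's effect estimates are biased. They are not: the intent-to-treat total effect does not depend on how a pre-randomisation variable is labelled, and adjusting for such a variable leaves the effect unbiased.
- That the planned adjustment will remove part of the treatment effect. This would need a school measure taken after randomisation, changed by the programme, and conditioned on in the main model. The article describes no repeat of the school survey and no such model. Had there been one, with quality explaining 30% of the variance and shifted by an assumed 0.25 or 0.5 SD, the simulated adjusted effect would fall from about −1.18 to −0.96 or −0.73 days. That is a reason for a safeguard, not a fault in the plan as written.

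**Conclusion.** The role given to the school quality measures is wrong as written. If they were taken before randomisation, as the article strongly implies, they cannot mediate, and their expected indirect effect is zero. That conclusion rests only on the timing. The illustrative spread of 0.11 to 0.18 day rests further on an assumed correlation of 0.3 to 0.5 and a cross-sectional outcome; under the simulation's different assumptions it is 0.13 to 0.28 day. In either case it is smaller than the unadjusted standard error of the arm effect, about 0.39 to 0.40 day. The consequence is confined to the mechanism analysis and to the description of these variables. The correction is worth making because it is cheap and because proper use of the same data can improve precision.

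**What to change.** Replace the mediator wording in Research instruments with a statement that the school quality measures, named individually and dated, are pre-intervention covariates and exploratory effect modifiers. State how they enter each model:

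- In an endline or baseline-adjusted comparison of arms, as covariates.
- In individual fixed-effects or difference-in-difference models, as measure-by-time terms for adjustment and arm-by-time-by-measure terms for exploratory modification.
- Any school measure collected after randomisation stays out of the primary intent-to-treat model. School pad provision is the clearest case: the Sanitary pads section says schools agreed to give government pads only to girls outside the project, so the programme itself may change that item.

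The cost is a sentence or two of analysis wording on data already collected, a few extra model terms, and some exploratory tests that must be labelled as such.

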### Study outcomes and hypotheses

The overall goal of the project is to determine the impact of Menstrual Health Management (MHM) interventions on girls’ well-being and education. The main objective of this research will be to determine what is the effect of an MHM intervention combining empowerment (reproductive health education) and products (sanitary pads) approaches on girls’ well-being and education, versus empowerment or products alone. The outcomes of interest include both short-term indicators of education and reproductive health and well-being, as well as long-term indicators, as shown in Table 2.

**Table 2 Tab2:** Key Study Indicators

Key Indicators	Well-Being	Education
Short-term	- Sexual and reproductive health rights (SRHR) knowledge and attitudes - Menstrual health knowledge and attitudes - Gender norms - Self-efficacy	-School attendance -School participation/engagement
Long-term	- Experience of unwanted sex - Timing of first sex - Timing of pregnancy	-School retention -Performance in school

As shown in Fig. 2, the project’s theory of change hypothesizes that the Nia brand disposable sanitary pad distribution will increase the use of pads to manage menstruation, which will lead to an increase in two short-term education indicators: 1) school attendance, and 2) participation / engagement in class. The bottom panel of the figure shows the hypothesized impact of the reproductive health education component on key short-term indicators of girls’ social and personal competencies: 1) sexual and reproductive health and rights (SRHR) knowledge and attitudes, including menstrual health knowledge and attitudes, 2) gender norms, and 3) self-efficacy. This conceptual framework is based on Lloyd’s [27] typology of competencies (e.g., knowledge, skills attitudes and values) that basic education should incorporate in order to empower adolescent girls. According to this typology, social competencies include pro-social values (i.e. attitudes that are positive and/or beneficial for others and society), respect for human rights and gender consciousness, while personal competencies include self-esteem, reproductive health knowledge and management skills and self-protective skills.

**Fig. 2 Fig2:**
[figure not shown]
Nia Project Theory of Change

The combination of the two intervention components is hypothesized to synergistically increase the effect size for all outcomes, which could potentially affect longer-term outcomes, such as school retention, reduced unwanted sex, delayed pregnancy and delayed first sex. While this study is powered to detect changes in the short-term indicators, additional analyses will be conducted to determine whether girls observed short-term improvements are associated with longer-term impacts.

### Analysis plan

The program evaluation of the Nia Project will examine the effect of the average treatment across study arms while identifying the causal mechanisms driving that impact. Using intent-to-treat analysis, all girls in the original sample randomized to study arms will remain part of the study despite non-compliance, protocol deviations, withdrawal, or anything else that happens after randomization. Econometric estimation techniques such as fixed effects estimation will be applied to control for unobserved time invariant individual characteristics. The evaluation will compare the average increase in outcomes of girls in intervention arms to the average increase in outcomes of girls in the control arm. Additional hypotheses will be tested using difference in difference analysis to understand both causal mechanisms among girls who received the interventions and the potential effect of improvements in short-term indicators on longer-term outcomes. The rich dataset will provide an extensive list of variables that can be adjusted for directly in the analysis. The results will be triangulated using qualitative data.

To examine balance across study arms following randomization, multinomial logistic regression models were estimated using each dataset to test for joint orthogonality for a selected list of indicators, comparing each treatment group with the control group. For the school quality dataset, the variables included were: school performance by gender, number of toilets, distribution of pads and availability of pads in stock. The results showed that there were jointly no significant differences between study arms (*p* = .60). For the girls’ dataset, indicators included were: ever repeated a grade, age at starting school, self-efficacy scale, decision-making scale, gender-norms scale, reproductive health knowledge score, ever menstruated, justification of violence, experience of symptoms of reproductive health infections and ever had sex. The results showed that there were jointly no significant differences between study arms (*p* = 0.14).

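### The mechanism analyses, if done by actual receipt and by short-term improvement, condition on post-randomisation variables, so they are open to bias in the programme's favour and do not support causal wording

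*Protocol article*

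**What the plan says.** The Analysis plan sets an intention-to-treat analysis in which "all girls in the original sample randomized to study arms will remain part of the study despite non-compliance, protocol deviations, withdrawal". Its main contrast, of intervention arms against the control arm, follows: "The evaluation will compare the average increase in outcomes of girls in intervention arms to the average increase in outcomes of girls in the control".

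The next sentence changes both the purpose and the population: "Additional hypotheses will be tested using difference in difference analysis to understand both causal mechanisms among girls who received the interventions". It continues with a second target, "the potential effect of improvements in short-term indicators on longer-term outcomes". The section's opening sentence states the ambition in causal terms: "while identifying the causal mechanisms driving that impact".

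Two safeguards are named. One is that "fixed effects estimation will be applied to control for unobserved time invariant individual characteristics". The other is adjustment for measured variables, which are not listed.

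Two other places bear on the point. Research instruments says: "The endline survey will include additional questions to measure exposure to interventions". Study outcomes and hypotheses (text after Fig. 2) describes the second analysis more cautiously: "additional analyses will be conducted to determine whether girls observed short-term improvements are associated with longer-term impacts".

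**The concern.** Receipt and short-term improvement both happen after randomisation, so randomisation does not balance receivers or improvers against anyone else. The education component is offered to girls enrolled in school (Methods/design, opening paragraph), in clubs held in school time (Reproductive health education). Attendance and retention are study indicators (Table 2). A girl who drifts out of school therefore receives less and also does worse on these outcomes, whether or not the programme works. Control girls cannot be sorted in the same way.

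At stake is how secondary results are read. A receiver analysis could show a benefit where the randomised comparison shows none, and the section's wording would allow it to be called a causal mechanism.

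**Working it through.** **1. The wording.** The main contrast refers to girls in intervention arms. The next sentence refers to girls who received the interventions, and the endline survey will measure exposure. Analysis by actual receipt is thus the more natural reading, but no sentence links the exposure questions to this analysis.

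**2. What differencing leaves behind.** Let p be the share of intervention-arm girls counted as receivers, and Δ a girl's change from baseline to endline. With no true effect, mean Δ in the control arm equals p·E[Δ | receiver] + (1 − p)·E[Δ | non-receiver]. Hence

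receivers minus all controls = (1 − p) × (E[Δ | receiver] − E[Δ | non-receiver]).

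This is zero if receivers and non-receivers share the same untreated trend. Otherwise it is not zero, and fixed effects do not remove it.

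**3. Retention.** All sampled girls were in Class 7 at baseline, so baseline enrolment does not vary and difference-in-differences reduces to an endline comparison. Suppose a fraction d leaves school in every arm and only girls still in school count as full receivers. Retention is then 1 among receivers and 1 − d among controls, a difference of d with no effect at all.

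**4. The yardstick.** The only scale for attendance in the article is the detectable difference of 1.18 days missed per four weeks (Sample size calculations). With 35 schools × 20 girls per arm, ICC 0.173 and SD 3.57, the design effect is 1 + 19 × 0.173 = 4.287. The standard two-sided formula gives (1.960 + 0.842) × 3.57 × √(2 × 4.287/700) = 1.107. So 1.18 is not reproduced exactly. The point does not depend on it, and 1.18 is used below only for scale.

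**5. Illustrations. All inputs are assumed; none is in the document.**

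- Formula in step 2: 20% non-receivers and a trend gap of 1 day give 0.2 × 1 = 0.2 day. 40% and 2 days give 0.4 × 2 = 0.8 day. Divided by 1.18, these are 17% and 68%. The range only restates its inputs.
- Simulation of a two-wave trial with zero true effect (35 × 20 per arm, ICC 0.173, SD 3.57, about 75% receipt). Receipt falls with a fixed trait (weight 0.5) and with a time-varying factor (weight 1), plus unit noise, with a cut-off at −1. The time-varying factor also lowers short-term improvement by 0.5 per SD and adds b days missed per SD. Negative values are spurious benefits.

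| b (days per SD) | All girls | Receivers vs all controls | Slope per unit of short-term improvement |
|---|---|---|---|
| 0 | 0.01 | 0.01 | 0.00 |
| 0.25 | 0.00 | −0.07 | −0.11 |
| 0.5 | 0.00 | −0.14 | −0.20 |
| 1.0 | 0.00 | −0.28 | −0.40 |

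Hand check: the latent SD is √(0.25 + 1 + 1) = 1.5, so receipt is Φ(0.667) = 0.75 and the receiver bias is −b × (1/1.5) × 0.319/0.748 = −0.285b. The slope is −0.5b/1.25 = −0.4b. Both agree with the table.

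The first row matters as much as the others: when selection runs only through fixed traits, neither analysis shows bias beyond simulation error.

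**6. Time order.** Knowledge, gender norms and self-efficacy are measured by survey, at baseline and at one endline after 18–21 months. When within that interval they changed is not observed, so a change in them cannot be placed before a longer-term outcome. Attendance is different: it is tracked separately from the surveys (Cluster randomized study design).

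**The case against.** The strongest reply is that the receivers-versus-controls contrast is inferred. The opening of Methods/design describes the whole beneficiary cohort as receiving interventions, so the disputed phrase may simply mean girls in the intervention arms. On that reading the first analysis conditions on nothing after randomisation. This possibility stands, and it is why the wording needs clarifying. It does not help the second analysis, since short-term improvement is post-randomisation on any reading.

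Several further limits also stand:

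- Difference-in-differences is unbiased under parallel trends, and adjustment for measured variables is planned. A reader might infer that the estimates are biased; the document supports only that they are open to bias.
- A reader might infer a bias of 0.2 to 0.8 day. The article gives neither a receipt share nor a trend gap, so no figure measures bias in this trial.
- A reader might infer that no short-term indicator can be shown to precede a longer-term one. That fails for tracked attendance.
- Dependence on schooling is documented for the education component. For pads, the article says only that each girl gets a monthly packet.
- The analyses are labelled additional, and Study outcomes and hypotheses already uses associational wording for the second one.

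It can also be said that assumptions and sensitivity analyses belong in a fuller plan. That is fair for missing detail. Here, however, the article itself names the method and the population and attaches the causal label.

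**Conclusion.** The point holds in a limited form. Read as an analysis by actual receipt, the planned difference-in-differences conditions on a post-randomisation variable that, for the education component, depends on staying in and attending school. The analysis of short-term improvement conditions on a post-randomisation variable as well. The fixed effects address only time-invariant differences. The likely direction of bias favours the programme, and the risk is clearest for retention.

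The size is unknown. Under the assumptions shown, the spurious benefit in days missed runs from none (selection on fixed traits only) through 0.07 to 0.28 day in the simulation, to 0.8 day at the upper assumed corner. The intention-to-treat comparison is untouched, so this concerns the claims made from secondary analyses and not the trial's main result. Within the article, the causal and effect wording of the Analysis plan goes further than the associational wording of Study outcomes and hypotheses, and the two should agree.

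**What to change.** 1. State whether girls who received the interventions means girls assigned to them or girls with measured exposure.
2. If the effect of receipt is wanted, estimate it by two-stage least squares with randomised arm as instrument for exposure, keeping all randomised girls and clustering standard errors by school. State the exclusion assumption: arm acts on the outcome only through the measured exposure. Say how girls absent from the endline survey, who have no exposure answer, are kept in.
3. Report the link from short-term to longer-term outcomes as an exploratory association, or as a mediation analysis based on randomised arm with sensitivity to unmeasured confounding. Limit claims about time order to indicators with dated measurements, such as tracked attendance.
4. Drop causal and effect wording for any analysis restricted to receivers or improvers.

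The cost is mainly text and analysis time, since exposure questions are already planned. The instrumental-variable estimate is less precise than an as-treated one. It gives the effect of receipt and does not by itself identify mechanisms.
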